**1. SUMMARY**

| **Study Title**: Comparison of anorectal biofeedback therapy delivered by home-based device with clinic-based anorectal manometry in patients with functional defecation disorders  **Aim:** To compare the treatment efficacy of anorectal biofeedback (clinical indicators and physiological parameters) performed with a novel home-based device with conventional therapies in patients with functional faecal incontinence.  **Site Location:**   1. GI Motility Clinic, Camden Hospital, NSW 2570 2. Advanced GI Surgery Unit, Royal Prince Alfred Hospital, NSW 2050   **Planned sample size:**   - Site 1: 40 participants (20 home-based with device, 20 clinic-based manometry) - Site 2: 80 participants (40 home-based with device, 40 clinic-based manometry)   **Inclusion criteria:** Males and females 18 – 65 years old, able to comprehend study and provide written consent. Diagnosed with a functional faecal incontinence and recommended for anorectal biofeedback therapy.  **Study procedures:**  A pilot feasibility study consisting of 40 participants will randomly assigned therapy with the novel device or anorectal manometry (conventional treatment). The conventional treatment group will receive 6 clinical training sessions with standard manometry (30 – 45 minutes each). While the test group will use the novel device at the clinic for 6 supervised training sessions, they may take the device home and continue training in between clinic sessions.  Upon completion of the feasibility study, a larger scale study (n=80) will be conducted. The test group will only receive one training session with the novel device and required to complete the rest of their training unsupervised at home.  **Study duration:** 3-years (36 months) |
| --- |

**2. BACKGROUND AND RATIONALE**

Anorectal biofeedback (BF) is a first-line rehabilitation therapy for the treatment of anorectal muscle disorders [1, 2]. These disorders cause 33% of chronic constipation and 60% of faecal incontinence [3, 4], two of the most prevalent gastrointestinal disorders, affecting 16% of the global population [5, 6]. BF therapy uses instrument-based “operant conditioning” (learning through repetition and reinforcement) to restore the normal muscle patterns for defecation. BF therapy is recommended by several consensus groups including the American and European Neurogastroenterology and Motility Societies [7]. Randomized clinical trials demonstrate BF efficacy of 75-89% in long-term symptom improvements [8, 9], and 83% reported improvements to quality-of-life [10]. Effective BF therapy demands regular attendance to a clinic over the treatment period of 6–8 weeks. Each session involves inserting a probe into the patient’s anal canal, which is then connected to a display for real-time visual feedback of muscle activities. Despite its benefits, BF is limited to few specialized clinics in tertiary hospital due to these challenges:

1. **Rising medical cost:** The high cost of equipment and technical staff required to deliver BF makes it difficult to establish clinics in regional and community hospitals.
2. **Time-consuming:** Average BF therapy involves the 6 weekly sessions and follow-up sessions after 6 and 12 months. Despite demand, clinics are limited by the number of patients they can treatment at one time.
3. **Adherence:** Difficulties accessing BF and the relative invasive nature of the procedure means fewer than 30% of patients are able to adhere and complete their prescribed treatment.

Anorectal manometry probes are the gold standard instrument for the diagnosis of functional anorectal disorders. Highly accurate sensors provide continuous and dynamic spatiotemporal mapping of anorectal pressures. Although this level of high fidelity data is not required for anorectal BF training, most clinics use the same manometry system due to ease of access [13]. However, these diagnostic systems are not well suited for BF therapy due to high setup and ongoing costs ($15K - $75K USD per system; $100 - $300 USD in consumables per use). In addition, the highly detailed data provided by these systems can be counterproductive in getting patient to understand their training.

Home-based BF with training devices has been proposed in the past [14-17]. Studies have demonstrated equivalent efficacy to office-based therapy while being more cost-effective. However, due to technical limitations, these past devices do not have the capabilities for therapists to remotely monitor and track patient compliance, which have significantly limited their adoption into clinical practice.

We have developed a new Internet-of-Medical-Things to deliver home-based BF. The system consists of an insertable probe with sensors to collect data on anal sphincter muscle contractility and rectal lumen pressures. The probe is wirelessly connected to a mobile app to provide real-time visual feedback of muscle activities to the user. The app records and processes training session data and clinical indicators (symptoms & bowel diary) from user input. Processed data will be sent to a cloud server to allow health providers to track progress and aid in decision-making. The proposed device will allow for instrumented anorectal BF training to be performed by patients at home.

**3. AIMS/OBJECTIVES/HYPOTHESES**

*Aim*

To compare the treatment efficacy of anorectal biofeedback (clinical indicators and physiological parameters) performed with a novel home-based device with conventional therapy options in patients with functional defecation disorders.

*Faecal incontinence is a heterogeneous condition, there is no single parameter to adequately define or represent an optimal way of assessing clinical outcomes. A range of subjective and physiological measures of bowel function are used as outcomes measures.*

*Site 1 Specific* - A feasibility assessment at Site 1 will evaluate the accuracy and repeatability of the prototype (V2) against anorectal manometry*

1. *Evaluate the capability of experimental device to generate anorectal exercise profiles*
2. *Compare the accuracy of experimental device against anorectal manometry*

*Site 1 and Site 2*

*Subjective primary outcome measures*

1. *Vaizey and Wexner faecal incontinence scores*
2. *Faecal incontinent episodes (days per week)*

*Objective primary outcome measure*

1. *Anal sphincter squeeze pressure (mmHg)*

*Secondary outcome measures*

1. *Anal sphincter resting pressure (mmHg)*
2. *Patient’s own view of effectiveness rating (“worse”, “same”, “improved”, or “cured”) and rating of that change in an ordinal scale of – 5 to + 5*
3. *Frequency of bowel motions and symptoms*
4. *[Experimental device group] Usability interview – 1. Ease of use, 2. Clarity of instructions, 3. Ease of cleaning, 4. Any additional Issues*

Hypotheses

We hypothesised that instrumented home BF therapy with the novel device is as efficacious as clinic-based BF therapy

**5. RESEARCH PLAN/STUDY DESIGN**

Randomised controlled trial – Phase 0/Pilot study

**5.1 Type of study:** Prospective clinical research

**5.2 Expected study duration:** The start time is anticipated to be 01 April 2022 with completion of the project expected to be 31/3/2024. The length of the study is expected to last for 3 years.

**5.3 Data source and Population**

*Study population and size*

The Site 1 feasibility study will be a pilot study involving n=15 (n=20 with 33% dropout) participants per group. This study will evaluate the capability of the experimental device to provide instrumented BF (create distinct BF exercise profiles and is understood by the user) and compare the data against anorectal manometry. This is similar to our previous study [18] but will use the new prototype (V2) and be in a patient population.

The data from this site will not be analysed together with data from Site 2, given the differences in methodology. However, data from Site 1 will be used to improve the statistical analysis plan for Site 2. Currently, the power calculations for Site 2 are based on a previous study [19], but data from Site 1 will be integrated to improve the calculation of sample size and power for Site 2.

Site 2 sample size and power calculations

Based on a previous study of biofeedback treatment for faecal incontinence [19], we estimate that for assessing home-BF and clinic-BF efficacy with a sample size of 30 per group (n=40 with 33% dropout), the paired t-test at the 0.05 significance level can detect a mean change in anorectal function measure of at least 0.45 SD with 0.80 power. This corresponds to at least a mean decrease of 8 in Vaizey/Wexner faecal incontinence score, decrease of 0.6 in faecal incontinence episodes, and 40% increase in anal sphincter squeeze pressure.

For the non-inferiority study, based on changes in the primary outcome measures, with n=30 per study arm, the test for non-inferiority has 0.70 power to reject, at the 0.05 significance level, the null hypothesis that the mean change due to home-BF is smaller than clinic-BF by at least 0.44 SD in favour of he alternative hypothesis that mean changes due to home-BF is no more than 0.44 SD lower than clinic-BF (i.e. Ho: ΔHB-ΔOB<−0.44SD vs. Ha: ΔHB-ΔOB≤−0.44SD).

Using estimates from previous study [19], we consider home-BF no worse than or better than clinic-BF if the home-BF group had at least 9 point decrease in Vaizey/Wexner faecal incontinence score (11 for clinic-BF, SD=3), 0.95 days/week decrease in faecal incontinence episodes (1.1 for clinic-BF, SD=0.25), and 19 mmHg increase in anal sphincter squeeze pressure (25 mmHg for clinic-BF, SD=10).

*Data collection/Outcome measurements*

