**During biofeedback therapy**

- Participants keep a physical or digital bowel diary (bowel habits, stool consistency, symptoms)
- Participants keep a physical or digital food diary (meals, macro nutrients consumes, fibre consumed)
- The Vaizey and Wexner faecal incontinence score completed at the first and last appointment [20, 21]
- A the last appointment, participant provide self-evaluation of treatment efficacy and change [22]

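### Site 2's stated power of 0.70 and 0.80 is not delivered at 30 per arm, and the 33% dropout behind it is unsourced and not reconciled with the protocol's own completion figure

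*Protocol*

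**What the plan says.** The Summary plans "Site 2: 80 participants (40 home-based with device, 40 clinic-based manometry". Section 5.3 takes the evaluable number as 30 per arm, "with a sample size of 30 per group (n=40 with 33% dropout", and uses that number for both power statements:

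- Within group: "the paired t-test at the 0.05 significance level" is said to detect a "mean change in anorectal function measure of at least 0.45 SD with 0.80 power". Sidedness is not stated.
- Between groups: "the test for non-inferiority has 0.70 power to reject, at the 0.05 significance level", the null being that "the mean change due to home-BF is smaller than clinic-BF by at least 0.44 SD". The true difference assumed is not stated.

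No source is given for the 33%, and the same rate serves both arms. The only other completion figure in the protocol is in Section 2 (Background and Rationale, item on adherence). It says that, because of access difficulties and invasiveness, "fewer than 30% of patients are able to adhere and complete their prescribed treatment". Section 5.3 does not refer to it.

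On outcome timing, Section 5.3 has "The Vaizey and Wexner faecal incontinence score completed at the first and last appointment". Section 5.8 schedules repeat manometry at a clinic visit when treatment ends. Group A attends up to six sessions over two months, with no minimum. Section 5.3 also says that Site 1 data will feed into the Site 2 sample size and power.

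**The concern.** Group A receives the therapy whose poor completion Section 2 offers as a reason for developing the home device. A reader therefore expects Section 5.3 to say why loss would be only 33% in that arm, and why it would be the same in the home arm, where the access barrier is meant to be lower. Two of the primary measures, the incontinence scores and squeeze pressure, need a late appointment. Patients who stop attending could plausibly miss it.

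The clinic arm is the non-inferiority reference. If it is depleted more than planned, power falls, and the remaining clinic patients may be a selected benchmark. If the stated power is also too high at the planned number, an inconclusive result becomes more likely than the plan admits, and it could not readily be told apart from a shortage of evaluable patients.

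**Working it through.** **Inputs.** From Section 5.3: 30 evaluable and 40 enrolled per arm, 33% dropout, paired effect 0.45 SD, non-inferiority margin 0.44 SD, significance level 0.05. From Section 2: completion below 30%. Assumed here because they are not stated: true difference 0 for non-inferiority, and a one-sided test at 0.05 (0.025 shown for comparison).

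**Step 1: dropout arithmetic.** 40 × (1 − 0.33) = 26.8, so about 27 remain per arm, not 30. Keeping 30 requires 30 / 0.67 = 44.8, or 45. The 40 matches 30 × 1.33 = 39.9. Going from 40 to 30 is a loss of 25%.

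**Step 2: the stated 0.80 (paired test).** Noncentrality is 0.45 × √n, with n − 1 degrees of freedom. At n=30 it is 0.45 × 5.477 = 2.465.

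- One-sided 0.05, critical t 1.699: power 0.78 (normal approximation 0.79).
- Two-sided 0.05, critical t 2.045: power 0.66 (normal approximation 0.69).
- At n=27: 0.74 one-sided, 0.61 two-sided.

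So 0.80 is approached only with a one-sided test.

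**Step 3: the stated 0.70 (non-inferiority).** Noncentrality is 0.44 / √(1/n₁ + 1/n₂), with n₁ + n₂ − 2 degrees of freedom. At 30/30 it is 0.44 / √(2/30) = 1.704, against a critical t of 1.672 at one-sided 0.05. Power is 0.52. At one-sided 0.025 it is 0.39. Neither gives 0.70; by the normal formula that would take 49 per arm at one-sided 0.05.

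**Step 4: fewer clinic patients.** If the Section 2 figure applied in full to outcome data, at most 0.30 × 40 = 12 clinic patients would be evaluable. The 20 below is an assumed 50% completion.

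| Evaluable home / clinic | One-sided 0.05 | One-sided 0.025 |
|---|---|---|
| 30 / 30 | 0.52 | 0.39 |
| 27 / 27 | 0.48 | 0.35 |
| 30 / 20 | 0.44 | 0.32 |
| 40 / 12 | 0.37 | 0.26 |
| 30 / 12 | 0.35 | 0.24 |

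**Step 5: separating the causes (one-sided 0.05).** From the stated 0.70 to 0.516 at 30/30 is a gap of 18.4 points that owes nothing to dropout. From 0.516 to 0.353 at 30/12 is a further 16.3 points. With 40 home patients and 12 clinic patients, power is 0.372, which is 14.4 points below 0.516.

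**The case against.** A reader might infer that the two sections contradict each other and that only 12 of 40 clinic patients will finish. The documents do not support that, for these reasons:

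- Section 2 describes adherence to prescribed biofeedback in ordinary care, across anorectal disorders generally. The 33% is assumed loss of consented trial participants with faecal incontinence. Both can be true.
- Section 2 partly blames access. Trial patients have already been referred, attended for diagnostic manometry and consented, so some of that barrier is behind them.
- Six sessions is a ceiling, and the end-of-treatment manometry visit is not made conditional on sessions attended. Someone who attends three sessions and the final visit still supplies squeeze pressure. Incontinence episodes are a further primary outcome, and bowel diaries run throughout treatment. Nothing limits the analysis to completers.
- The Section 2 figure concerns existing delivery of biofeedback, so it does not bear on the home-arm paired test.

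All of this stands, and it makes 12 a conditional worst case. It does not supply a basis for the 33%, or for equal loss in both arms.

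A second tempting reading is that dropout explains the missing power. Step 5 shows otherwise: more than half of the gap from 0.70 to 0.35 is there at a full 30/30.

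It can also be said that the raw-unit criteria in Section 5.3, if read as margins, are wider: (11 − 9)/3 = 0.67 SD, (1.1 − 0.95)/0.25 = 0.60 SD and (25 − 19)/10 = 0.60 SD. Power at 30/30 is then 0.74 to 0.82 at one-sided 0.05. But the plan attaches its 0.70 to 0.44 SD, and at that margin the figure does not hold.

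Finally, one common dropout rate is ordinary planning practice, and the Site 1 update is already promised. That makes the fix smaller but does not remove the need for it.

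**Conclusion.** The concern holds as an unsupported planning assumption combined with power figures that are not delivered.

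- At the stated margin of 0.44 SD, non-inferiority power is 0.52 with 30 per arm and 0.48 with 27 per arm, against a stated 0.70.
- Paired-test power at 0.45 SD and n=30 is 0.78 one-sided or 0.66 two-sided, against a stated 0.80. If a one-sided test was meant, this shortfall is small.
- The 33% is unsourced, applied equally to both arms, and in unexplained tension with Section 2. Clinic-arm loss above it would bring non-inferiority power to 0.44 at 30/20, and to 0.35 at 30/12 if the Section 2 figure carried over fully to outcome data.

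The non-inferiority figures rest on a true difference of 0 and a one-sided 0.05 test; at 0.025 they are lower throughout. The 20 clinic patients are an assumption, and the 12 are conditional.

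**What to change.** In Section 5.3, under the Site 2 sample size and power calculations:

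1. Withdraw 0.70 and 0.80 as the power delivered.
2. Give the basis for the 33%, say whether dropout means missing outcome data or incomplete therapy, and explain how it relates to the completion figure in Section 2.
3. Restate power for both tests at the numbers that 40 per arm actually yields (about 27 at 33% loss), with sidedness, margin and assumed true difference stated. Cover a range of clinic-arm completion, for example 30%, 50% and 67%, and state home-arm completion separately.
4. Include clinic-arm outcome completion from Site 1 in the update already planned for Site 2. Only the clinic arm carries over, because the Site 1 home arm has up to six supervised sessions whereas Site 2 has one.

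The cost is a rewritten paragraph, a short recalculation and a less favourable stated power. No extra patients, visits or staff are asked for.

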**5.8 Study Procedure**

Patients arrive at a study site to undergo routine diagnostic anorectal manometry. If a patient is diagnosed with a functional faecal incontinence and suitable for BF therapy they will be asked to take part in this study. Randomization used permuted blocks of 4 with 1:1 assignment into the parallel study groups described in Section 5.3. Random numbers generated in advance and placed into sequentially numbered opaque envelopes, sealed and used for subject assignment. After screening, and once patients met the study inclusion and exclusion criteria, patients are enrolled into one of the treatment arms, by opening the sealed envelope. The therapist ([name] or [name]) and patient are not blinded to the treatment.

The specialist nurse therapist provides advice regarding bowel habits, exercise, laxatives, dietary fibre and fluid intake, and timed-toilet training during the initial consultation to all participants. The therapist will teach participants how to improve their push effort by using postural and diaphragmatic breathing techniques and instruct them to practice these manoeuvres at home for 15 minutes, three times a day.

*Clinic-based biofeedback using anorectal manometry*

In addition to the aforementioned general instructions, participants receiving clinic-based BF (**Group A**) will be attending a maximum of six in-clinic therapy sessions over 2 months. BF training uses the anorectal manometry. Manometry catheters have several circumferential pressure sensors that straddle the entire anal canal and a proximal sensor placed in the rectum, providing continuous and dynamic spatiotemporal mapping of anorectal pressures. During anorectal BF therapy, a sheath is placed over the catheter and inserted into the anal canal. The system and therapist provides provide visual/audio feedback to the patient and record exercise parameters to establish baseline or evaluate progress. The key BF manoeuvres are:

1. **Rest:** after probe placement, a period of time is given for the patient to relax such that anal sphincter tone returns to basal levels. Anal resting pressure is measured using the averaged resting pressure over the length of the anal canal over a period of 20 seconds. This pressure is a composition of the internal and external anal sphincter and, to a lesser extent, by the hemorrhoidal plexus.

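### The stated 33% dropout does not reconcile 40 enrolled with 30 evaluable per group at Site 2, or 20 with 15 at Site 1

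*Protocol*

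**What the plan says.** Section 5.3 of the protocol gives an evaluable number, an enrolled number and a dropout rate for each site. Site 2 is planned "with a sample size of 30 per group (n=40 with 33% dropout". Site 1 is planned with "n=15 (n=20 with 33% dropout) participants per group".

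The Summary confirms that the larger number in each pair is the number enrolled: "Site 1: 40 participants (20 home-based with device, 20 clinic-based manometry" and "Site 2: 80 participants (40 home-based with device, 40 clinic-based manometry". Allocation is 1:1 (section 5.8).

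Both Site 2 power statements in section 5.3 rest on 30 per group. The first says that at this size "the paired t-test at the 0.05 significance level can detect a mean change in anorectal function measure of at least 0.45 SD with 0.80 power". The second says that "with n=30 per study arm, the test for non-inferiority has 0.70 power to reject, at the 0.05 significance level", against a margin of 0.44 SD. Section 5.3 also says that Site 1 data will be used to refine the Site 2 sample size and power. Site 1 itself is described as a feasibility pilot, has no power calculation, and is not analysed together with Site 2.

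**The concern.** Dropout is a share of those enrolled. Read that way, the three figures given for each site cannot all be true: with 40 enrolled and 33% lost, 30 do not remain, and likewise for 20 and 15.

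The Site 2 power statements assume an evaluable number that the design does not deliver under its own dropout rate. Participants lost before the end of treatment would have no change value on two of the primary measures. The incontinence scores are completed at the first and last appointments (section 5.3), and the change in squeeze pressure needs the repeat manometry at the end of treatment (section 5.8). The same inflation step could also be carried into the planned re-sizing of Site 2.

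**Working it through.** **Inputs, all from section 5.3 and the Summary.** Site 2: 30 evaluable, 40 enrolled per group, dropout d = 0.33. Site 1: 15 evaluable, 20 enrolled per group, d = 0.33. Paired t-test: 0.45 SD, alpha 0.05, sidedness not stated. Non-inferiority test: margin 0.44 SD, alpha 0.05.

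**Reproducing the plan's enrolled numbers.**
- n × (1 + d): 30 × 1.33 = 39.9, so 40; 15 × 1.33 = 19.95, so 20. Both stated figures come back.
- n / (1 − d): 30 / 0.67 = 44.8, so 45; 15 / 0.67 = 22.4, so 23. Neither stated figure comes back.
- n / (1 − d) with d = 0.25: 30 / 0.75 = 40; 15 / 0.75 = 20. Both stated figures come back.

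The stated numbers therefore fit either the wrong inflation formula at 33% or the right formula at 25%.

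**Forward check.**
- 40 × (1 − 0.33) = 26.8, about 27, which is 3 short of 30.
- 20 × (1 − 0.33) = 13.4, about 13, which is 2 short of 15.
- Implied loss in the plan's pairs: (40 − 30)/40 = 25% and (20 − 15)/20 = 25%.
- Taking 33% as one third changes nothing: 26.7 and 13.3 remain, and 45 and 23 are still needed.

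**Effect on Site 2 power (noncentral t).**

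Paired t-test within a group: df = n − 1, noncentrality 0.45 × √n. This is 0.45 × √30 = 2.46 at n = 30, and 0.45 × √27 = 2.34 at n = 27.

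Non-inferiority, two independent groups, one-sided 0.05, true difference 0: df = 2n − 2, noncentrality 0.44 × √(n/2). This is 0.44 × √15 = 1.70 at n = 30, and 0.44 × √13.5 = 1.62 at n = 27.

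| Test | n = 30 | n = 27 | Loss |
|---|---|---|---|
| Paired t, 0.45 SD, two-sided 0.05 | 0.66 | 0.61 | about 5 points |
| Paired t, 0.45 SD, one-sided 0.05 | 0.78 | 0.74 | about 4 points |
| Non-inferiority, 0.44 SD | 0.52 | 0.48 | about 4 points |

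The n = 30 column does not return the protocol's 0.70 for non-inferiority. It comes near 0.80 for the paired test only if that test is one-sided. That is a separate question about the power calculation. The part due to the dropout figure is the last column only.

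**The case against.** Several points on the other side are fair.

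- **The cause is not documented.** It is tempting to say that the authors multiplied by 1.33. The protocol shows no formula, and a 25% rate mislabelled as 33% fits equally well. So does a loose use of 33% for the recruitment margin over the evaluable number (10/30 and 5/15). On these readings 40 to 30 and 20 to 15 are coherent and only the label is wrong. This stands as to cause. It does not remove the inconsistency, because the text calls the figure dropout and gives no other definition.
- **The effect is small.** This stands. A reader might set the stated non-inferiority power of 0.70 beside 0.48 and put the whole gap down to dropout. That is not supported: 0.52 is already what 30 per arm gives under the assumptions above.
- **Site 2 numbers are provisional.** This stands and lowers the consequence, but the figures as written still need correcting before they feed the recalculation.
- **Site 1 loses nothing that was claimed.** This stands. A reader might infer that Site 1 is underpowered, but no power or decision rule there depends on 15 rather than 13.

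A stronger reading would use the Background, which says "fewer than 30% of patients are able to adhere and complete their prescribed treatment", to argue that 33% is far too optimistic and that only about 12 of 40 per arm would be evaluable (40 × 0.30). The documents do not support this. The Background figure describes completion of prescribed treatment, attributed there to poor access and invasiveness, and forms part of the rationale for the home device. It is not a rate of missing trial outcomes, and a participant who stops training early can still attend for end-of-treatment measurements.

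**Conclusion.** The concern holds as an internal arithmetic inconsistency at both sites. At 33% dropout the planned enrolment leaves about 27 evaluable per group at Site 2 and about 13 at Site 1; the stated 30 and 15 correspond to 25% dropout. For Site 2 the cost is about 4 to 5 points of power on each of the two tests that the protocol sizes. For Site 1 only the stated evaluable number is wrong.

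The forward check needs only the protocol's figures and the ordinary meaning of dropout. The power losses assume that participants who drop out contribute no change value, that dropout is equal in the two arms, and, for non-inferiority, a one-sided 0.05 two-sample t-test with no true difference. The wrong-formula explanation is a plausible inference, not a finding. This is a modest correction that should be made because both Site 2 power statements rely on the figure.

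**What to change.** Leave enrolment at 40 and 20 per group and make one of two changes in section 5.3:

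1. State the tolerated dropout as 25%, so that 30 and 15 evaluable follow from 40 and 20; or
2. Keep 33%, restate the evaluable numbers as 27 (Site 2) and 13 (Site 1), and recompute both Site 2 power statements at 27 per group.

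The choice depends on which rate the investigators actually expect, which the protocol does not settle. In either case, use n/(1 − d) when the Site 2 size is recalculated from Site 1 data.

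The cost is restated figures in one section, with no change to enrolment or procedures. Keeping both 33% dropout and the full 30 and 15 evaluable would instead need 45 and 23 per group, that is 90 rather than 80 participants at Site 2 and 46 rather than 40 at Site 1.

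### The detectable change of 0.45 SD cannot equal 8 score points and 0.6 episodes under the SDs of 3 and 0.25 that the same section takes from the same study

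*Protocol*

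**What the plan says.** All the figures are in Protocol section 5.3, under the Site 2 sample size and power calculations.

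- **Test and size.** The calculation is made "with a sample size of 30 per group (n=40 with 33% dropout"). It uses "the paired t-test at the 0.05 significance level", with no statement of one or two sides.
- **Detectable effect.** The test "can detect a mean change in anorectal function measure of at least 0.45 SD with 0.80 power".
- **Conversion to raw units.** "This corresponds to at least a mean decrease of 8 in Vaizey/Wexner faecal incontinence score, decrease of 0.6 in faecal incontinence episodes", and a "40% increase in anal sphincter squeeze pressure".
- **SDs, two paragraphs later.** For the score: "9 point decrease in Vaizey/Wexner faecal incontinence score (11 for clinic-BF, SD=3"). For episodes: "0.95 days/week decrease in faecal incontinence episodes (1.1 for clinic-BF, SD=0.25"). For squeeze pressure the paragraph gives increases of 19 mmHg (home) and 25 mmHg (clinic) with an SD of 10.

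Both paragraphs cite reference [19] as their source. The section also calls the power calculations current and says Site 1 data will be used to refine them.

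**The concern.** The conversion sentence restates a standardised effect in raw units, so dividing each raw figure by 0.45 must return the SD used for planning. The SDs it returns are several times those in the later paragraph. The score and the episode count fail by similar factors, so a single misprint is an unlikely explanation.

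The outcomes concerned are primary outcomes in section 3. The later paragraph uses its SDs beside the raw differences by which home therapy would be judged no worse than clinic therapy. If those SDs were wrong, the raw differences would be far smaller in SD units than they appear, and 30 per arm would say little about them. If the raw figures in the conversion sentence were wrong, the reader is misinformed about what the paired test can detect, and nothing else changes. The protocol leaves the reader unable to tell which applies.

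**Working it through.** **Inputs (Protocol section 5.3).** n = 30 evaluable per group; level 0.05, sidedness not stated; power 0.80; detectable effect 0.45 SD; raw equivalents 8 points, 0.6 episodes and 40%; SDs 3 points, 0.25 days/week and 10 mmHg. The SDs are written beside mean changes, so I read them as SDs of change; the protocol labels them only as SD.

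**Step 1: reproduce 0.45 SD.** For a paired test by normal approximation, the detectable effect is (z for the level + z for the power)/√n.

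- One-sided: (1.645 + 0.842)/√30 = 0.454. This reproduces the plan's figure.
- Two-sided: (1.960 + 0.842)/√30 = 0.51.

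Exact values come from the noncentral t distribution with n − 1 degrees of freedom:

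| n | Sides | Normal approximation | Exact t |
|---|---|---|---|
| 30 | one | 0.454 | 0.465 |
| 30 | two | 0.51 | 0.53 |
| 40 | one | 0.393 | 0.400 |
| 40 | two | 0.443 | 0.454 |

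Power at 0.45 SD with n = 30 is 0.794 (one-sided normal), 0.777 (one-sided t) or 0.664 (two-sided t).

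**Step 2: the SDs that the conversion implies.** Implied SD = raw change / 0.45.

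- Score: 8/0.45 = 17.8, against a stated 3. Ratio 17.8/3 = 5.9.
- Episodes: 0.6/0.45 = 1.33, against a stated 0.25. Ratio 1.33/0.25 = 5.3.

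**Step 3: the same check in the other direction.**

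- 0.45 SD in raw units is 0.45 × 3 = 1.35 points, 0.45 × 0.25 = 0.11 days/week and 0.45 × 10 = 4.5 mmHg.
- In SD units, 8 points is 8/3 = 2.67 SD and 0.6 days/week is 0.6/0.25 = 2.40 SD.
- The 40% squeeze figure cannot be checked, because no baseline is given. A rise of 4.5 mmHg is 40% only of a baseline of 4.5/0.40 = 11.25 mmHg.

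**Step 4: can sidedness or n explain it?** The table spans about 0.39 to 0.53 SD.

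- At 0.53 SD the implied SDs are 15.1 and 1.13, still 5.0 and 4.5 times the stated values.
- At 0.40 SD they are 20 and 1.5, or 6.7 and 6.0 times.

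No row brings the two sets together.

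**Step 5: consequences on each branch.**

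*SDs of 3 and 0.25 are right.* The paired noncentrality is 2.67 × √30 = 14.6 for 8 points and 2.40 × √30 = 13.1 for 0.6 days/week, so power is essentially 1. Only the conversion sentence is wrong. The raw non-inferiority differences are (11 − 9)/3 = 0.67 SD and (1.1 − 0.95)/0.25 = 0.60 SD, with power 0.82 and 0.74 at 30 per arm (one-sided 0.05, t-test, no true difference).

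*SDs of 17.8 and 1.33 are right.* The same raw differences are 2/17.8 = 0.11 SD and 0.15/1.33 = 0.11 SD. Power is Φ(0.1125 × √15 − 1.645) = Φ(−1.21) = 0.11.

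**The case against.** **The raw figures may be expected effects.** The 8 points, 0.6 episodes and 40% could be changes anticipated from the earlier study rather than detectable limits. That is possible, and it is the benign explanation. The sentence nevertheless presents them as the equivalent of 0.45 SD, so it would still need rewording.

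**A different SD may be meant.** A baseline SD would differ from an SD of change. But a paired t-test runs on the SD of change, and the section does not say that another SD was used.

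**The formal non-inferiority margin is 0.44 SD.** Power at a margin set in SD units does not depend on the raw SD. This stands. The figure of 0.11 applies only to the raw differences of 2 points and 0.15 days/week, and only on one branch.

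**The numbers are provisional.** The plan to update them from Site 1 lowers the urgency, but the contradiction remains in the text until it is corrected.

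**Stronger readings that the protocol does not support.**

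- A reader might infer that paired power is 0.66 rather than 0.80. That presupposes a two-sided test with 30, which the protocol never states. The 0.45 SD figure does reproduce one-sided, so what is shown is an unstated assumption and not an error.
- A reader might infer that the sidedness question causes the SD discrepancy. It does not: 0.53 against 0.45 is a factor of about 1.2.
- A reader might infer that 3 and 0.25 are standard errors entered as SDs. Nothing in the protocol bears on this, and the source study is not at hand.

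**Conclusion.** The point holds as an internal contradiction. Section 5.3 uses two incompatible sets of SDs for two primary outcomes, 5.9-fold apart for the score and 5.3-fold for episodes, and attributes both to one study. This rests only on the section's own figures and on reading the stated SDs as SDs of change.

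It would be tempting to conclude that the planning SDs are wrong, or that the non-inferiority comparison has almost no power. The protocol supports neither, because it does not show which set is in error. On one branch a single sentence is wrong and the paired test has ample power. On the other, power for the raw differences is about 0.11, assuming 30 per arm, one-sided 0.05 and no true difference between arms.

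Sidedness is a secondary clarification. With n = 30, the 0.45 SD figure holds only as a one-sided normal approximation.

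**What to change.** 1. Recheck the cited study and state one SD of change for each outcome, labelled as such. Use it in both the paired and the non-inferiority paragraphs.
2. Correct the conversion sentence in one of two ways. Either replace the raw figures with the detectable effect multiplied by that SD (with the present SDs and 0.45 SD: 1.35 points, 0.11 days/week and 4.5 mmHg), or relabel 8, 0.6 and 40% as expected effects and give the squeeze baseline behind the percentage.
3. State the sidedness with the detectable effect. With 30 per group, the exact t-test gives 0.465 SD one-sided or 0.53 SD two-sided.
4. If the larger SDs prove right, recompute power for the raw non-inferiority differences before Site 2 begins.

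The cost is one source check and an amendment to a few sentences of section 5.3. The planned Site 1 update is a natural occasion. The stated power may fall if the larger SDs are confirmed.
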